# The impact of a blend of *Pistacia atlantica* seed and canola oil compared with a blend of corn-canola oil with synthetic antioxidant and corn-canola oil without synthetic antioxidant on oxidative stress markers in patients with metabolic syndrome: protocol for a triple-blind, randomized, three-way cross-over clinical trial

**DOI:** 10.1186/s13063-023-07269-1

**Published:** 2023-07-24

**Keywords:** *Pistacia atlantica* oil, Corn oil, TBHQ, Metabolic syndrome, Antioxidant, Oxidative stress

## Abstract

**Background:**

Metabolic syndrome (MetS) is regarded as a complex metabolic disorder. Recently, the role of dietary antioxidants in the underlying pathogenesis and complications of MetS has come into focus. *Pistacia atlantica* oil is known as a high antioxidant oil which might improve the antioxidant status of dietary oils and also oxidative stress markers. On the other hand, tert-Butylhydroquinone (TBHQ) is an approved food-grade synthetic antioxidant that acts both as an inducer and inhibitor of carcinogenesis. The current trial will explore the possible effect of a blend of *Pistacia atlantica* seed-canola oils, corn-canola oils with TBHQ, and corn-canola oil without TBHQ on oxidative stress markers in patients with MetS.

**Methods:**

We will conduct a single-center, triple-blind, three-way randomized cross-over clinical trial (RCT) among 72 patients with MetS. After a 1-month run-in period, eligible participants will consume the intervention oils as their regularly consumed oils in a random order. Each intervention period will last 8 weeks separated by 4-week washout periods. Anthropometric indices, body composition, physical activity, blood pressure, and 24-h dietary food recall measurements will be assessed at the beginning and the end of each intervention period. The primary outcome will be oxidative stress markers including serum total antioxidant capacity, total oxidant status, malondialdehyde, nitric oxide, and the enzyme activity of myeloperoxidase, superoxide dismutase, catalase, glutathione peroxidase, and glutathione reductase. The secondary outcomes will be changes in MetS components including blood pressure, fasting blood glucose, triglyceride, high-density lipoprotein cholesterol, and anthropometric measurements.

**Discussion:**

*Pistacia atlantica* seed oil is high in antioxidants. An intervention with this oil could offer an option for oxidative stress prevention among patients with metabolic syndrome. The present clinical trial will be the first one assessing the impact of *Pistacia atlantica* oil on human oxidative stress markers.

**Trial registration:**

Iranian Registry of Clinical trials IRCT20130223012571N8. Registered on 4 March 2022.

## Strengths and limitations

The first trial regarding the impact of *Pistacia atlantica* seeds oil on oxidative stress markers in humans.A triple-blind randomized controlled trial to assess the effects of three dietary vegetable oils.Bio-banking of blood components provides the opportunity to investigate the effect of dietary oils on different aspects of human health.The single-center design of the study limits the generalization of results to all populations.

## Introduction

*Pistacia atlantica* is a plant that grows in the Mediterranean region and the Middle East. The seeds are high in phytochemicals with antioxidant properties like α-pinene (20.8%), camphene (8.4%), myrcene (8.2%), and limonene (8%) [1, 2]. Also, its antimicrobial activity against both Gram-positive and negative bacteria was investigated [3]. In addition, it is proposed that *Pistacia atlantica* seed oil is a healthy oil with high amounts of omega-3 fatty acids [4].

Metabolic syndrome (MetS) is a set of conditions including obesity, dyslipidemia, increased blood pressure, and hyperglycemia [5]. This syndrome affects 33% of the adult population in the USA [6]. The condition affects about 18.7 million Iranians according to ATP ΙΙΙ definitions [7]. The pathogenesis of MetS is complex and unclear yet. It is proposed that this condition is stemmed from modern lifestyle and can increase the risk of type 2 diabetes, cardiovascular disease, cancer, and premature mortality [8–11]. There is ample evidence regarding the role of oxidative stress (OS), a condition in which there is an impaired balance between the production of reactive oxygen and nitrogen species and enzymatic and nonenzymatic antioxidant system defense capacity [12, 13], in insulin resistance and inflammation as the main pathogenic mechanisms of MetS [14]. Recent studies have demonstrated that diets rich in foods with high antioxidant content including fruits, vegetables, and whole grains, as well as diets low in animal fat, might improve the OS status [15, 16].

It was shown that *Pistacia atlantica* seed oil might help in preserving fatty acids that are prone to oxidation. For instance, *Pistacia atlantica* oil has been used as a natural alternative for stabilizing kilka fish oil [17]. Some animal studies have also explored the antioxidant effects of *Pistacia atlantica* on animals with colitis, peptic ulcer, diabetes, and MetS [1, 18–21]. A study on mice with diabetes showed significant improvements in lipid profile, OS, and inflammation markers after 3 weeks of intervention with *Pistacia atlantica* oil [18]. Another study on diabetic rats also illustrated a significant decrease in malondialdehyde (MDA) and increased GSH, GPx, CAT, and SOD after treatment with *Pistacia atlantica* oil [1]. On the other hand, tert-Butylhydroquinone (TBHQ), an approved food-grade synthetic phenolic antioxidant, is widely used as a preservative in many food products including vegetable oils [22, 23]. It is shown that TBHQ might have genotoxic effects; this is while other studies have revealed that it inhibits carcinogenesis [22, 24]. The permissible level of TBHQ in fats and oils is 0.02% or 200 mg/kg of fat or oil [25]. This level is low but many people consume appreciable amounts of phenolic antioxidants as food additives from dietary sources that typical consumption is likely to exceed the allowed daily intake (ADI, 0–0.2 mg/kg) [25].

To the best of our knowledge, no previous studies have examined the effects of *Pistacia atlantica* seed oil on oxidative stress in Humans. Furthermore, no study has tried to investigate if this oil improves oxidative stress when compared with conventional healthy oils available in the market in which TBHQ is used as the preservative. For this purpose, the present study was designed to examine the effect of a blend of *Pistacia atlantica* seed oil and canola oil compared with a blend of corn and canola oil with TBHQ (as a sample of conventional vegetable oils available in the market) and a blend of corn and canola oil without TBHQ (as a control oil) on oxidative stress markers in patients with MetS.

## Methods and analysis

### Study design and population

This trial is a single-center, triple-blind, randomized, superiority, three-way cross-over clinical trial (RCT) among 72 patients with MetS. Eligible participants will consume a blend of *Pistacia atlantica* seed (20%) and canola oil (80%), a blend of corn (20%) and canola oil (80%) with TBHQ (75 ppm), and a blend of corn (20%) and canola oil (20%) without TBHQ after a 4-week run-in period. We aim to replace the oils regularly used at home with intervention oils. As all family members will receive the intervention oils, all data will also be collected for the spouses of the participants. The intervention periods will last 8 weeks and will be separated with 4-week washout periods in which sunflower oil will be provided for the participants. Sunflower oil is highly consumed among Iranian families as the main cooking oil [26]. The trial will be conducted in the Nutrition and Food Security Research Center, Shahid Sadoughi University of medical science, Yazd, Iran. We used standard protocol items for randomized trials (SPIRIT) as a framework for reporting this study protocol [27].

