### Recruitment and eligibility assessment

Recruitment will be taken place using advertisements and announcements at Endocrinology and Metabolism clinics and polyclinics of Shahid Sadoughi University of medical sciences, Yazd, Iran. The incidence of MetS in Yazd province is 56.1% [28]. The screening visit will be conducted by trained researchers for interested volunteers. During the first visit, the study procedure will be explained to participants, and informed consent will be obtained. Then, a questionnaire on socio-demographics and a 24-h physical activity recall will be completed for the participants. Also, anthropometric measurement, body composition, blood pressure measurement, laboratory assessment, and a 24-h food recall will be performed on the first visit by a trained nutritionist. Researchers will recommend the participants to maintain their physical activity all over the study period.

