### Exclusion criteria

Individuals reporting a history of cardiovascular disease, diabetes mellitus, any type of cancer, pancreatitis, liver disease, kidney disease, gastrointestinal disorders, history of changes in blood sugar and lipid-lowering pills over the past 3 months, changes in gastrointestinal medications less than 30 days before enrollment, weight changes over 3 kg during the 2 months prior to the study, allergy or intolerance to foods that will be used for the intervention, using alcohol consumption, using medication for hemostatic regulation (other than aspirin), taking systemic corticosteroids including androgen, phenytoin, erythromycin, taking drugs for COVID-19 including remdesivir, Interferon, actemra, favipiravir in the last 3 months, being pregnant, having intention to become pregnant, giving birth in the last 12 months, taking Omega-3 supplements more than 1 g/day, smoking more than 20 cigarettes a day, and those reluctance to follow the study protocol will be excluded from this study.

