### Criteria for discontinuing or modifying allocated interventions

The intervention will be discontinued for participants in case of the occurrence of exclusion criteria and participants’ requests.

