### Blinding, randomization, and allocation concealment

The three intervention oils will be provided in the same shape, color, appearance, and odor and will be packed in the same bottles. Bottles will be blinded for researchers and participants and will be labeled with three codes (A, B, C) by an independent researcher. The codes will not be released until after the statistical analyses; therefore, neither the study participants nor the personnel nor the statisticians will be aware of the intervention oils. We do not anticipate any requirement for unblinding but if required, the trial manager and data coordinator will have access to group allocations and any unblinding will be reported.

We will use a stratified block (with a block size of 6) randomization in which the stratification will be done based on sex. Then, the participants in each block will be randomly assigned to one of the 6 sequences of the rolling process to consume the three intervention oils during the study period (ABC, ACB, BAC, BCA, CAB, or CBA; Fig. 1). To ensure that all the subjects receive treatments in a balance and random order, computer-generated random numbers will be used. The allocation sequence and randomization will be conducted by an independent researcher and will be concealed from the researchers. This will be done by putting the randomly assigned sequence of interventions for each participant in sealed opaque envelopes.

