### Intervention program

After the first visit, participants and their spouses will be entered into a run-in period for 4 weeks in which their regularly consumed oils will be replaced with sunflower oil. During the run-in period, the participants will be randomly assigned to one of the 6 rolling sequences (Fig. 1). The participants will be asked to replace the oils regularly used at home with the intervention oils. All measurements and blood sampling will be done at the beginning and the end of each intervention period, therefore, there will be 8 visits. The details of all measurements that will be conducted during each visit are provided in Table 1.

**Table 1 Tab1:** Details of study visits

Measured variables	Beginning of study	Beginning of the run-in period	Beginning of phase 1	End of phase 1	Beginning of phase 2	End of phase 2	Beginning of phase 3	End of phase 3
	Visit 1	Visit 2	Visit 3	Visit 4	Visit 5	Visit 6	Visit 7	Visit 8
**Eligibility criteria assessment**	*							
**Medical history**	*							
**Informed consent**	*							
**Nutrition counseling**	*							
**Medication use**	*	*	*	*	*	*	*	*
**Physical activity**	*	*	*	*	*	*	*	*
**24-h dietary recall**	*	*	*	*	*	*	*	*
**Anthropometric measurement**	*		*	*	*	*	*	*
Weight	*		*	*	*	*	*	*
Height	*		*	*	*	*	*	*
Waist circumference	*		*	*	*	*	*	*
Hip circumference	*		*	*	*	*	*	*
**Body composition indices**			*	*	*	*	*	*
Body fat mass			*	*	*	*	*	*
Lean mass			*	*	*	*	*	*
Visceral fat			*	*	*	*	*	*
**Blood pressure**	*	*	*	*	*	*	*	*
**Blood sampling**			*	*	*	*	*	*
**Biochemical assessment**			*	*	*	*	*	*
Fasting blood glucose (FBS)	*		*	*	*	*	*	*
Triglyceride (TG)	*		*	*	*	*	*	*
High-density lipoprotein (HDL)	*		*	*	*	*	*	*
Total antioxidant capacity (TAC)			*	*	*	*	*	*
Total oxidant status (TOS)			*	*	*	*	*	*
Malondialdehyde (MDA)			*	*	*	*	*	*
Myeloperoxidase (MPO)			*	*	*	*	*	*
Superoxide dismutase (SOD)			*	*	*	*	*	*
Catalase (CAT)			*	*	*	*	*	*
Glutathione peroxidase (GPX)			*	*	*	*	*	*
Glutathione reductase (GR)			*	*	*	*	*	*
Nitric oxide (NO)			*	*	*	*	*	*

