### Compliance

The intervention oils will be provided for the participants and their families. We will ask participants to bring back intervention oil bottles provided in the previous visit. Then, these bottles will be weighed. Furthermore, 3-day dietary recalls will be used to assess the compliance of the participants to the intervention protocol.

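### The study oils go to the whole household, but the allergy exclusion covers only people entering the study, so a volunteer with an allergic child is eligible as written

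*Protocol article*

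**What the plan says.** The protocol article describes delivery of the oils by household. Under Study design and population it states "We aim to replace the oils regularly used at home with intervention oils" and adds "As all family members will receive the intervention oils, all data will also be collected for the spouses of the participants". The Compliance section repeats this: "The intervention oils will be provided for the participants and their families".

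The safeguards are written for a smaller group:

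- **Recruitment and eligibility assessment:** "The screening visit will be conducted by trained researchers for interested volunteers".
- **Exclusion criteria:** the list is addressed to individuals who report a condition. One item is "allergy or intolerance to foods that will be used for the intervention". No child or other household member is named.
- **Criteria for discontinuing or modifying allocated interventions:** "The intervention will be discontinued for participants in case of the occurrence of exclusion criteria". The same sentence also allows stopping at a participant's request.
- **Intervention program:** "participants and their spouses will be entered into a run-in period for 4 weeks". The Discussion adds that spouses undergo the study procedures. Spouses are therefore arguably within reach of the eligibility rules.

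On masking, the section on blinding says "Bottles will be blinded for researchers and participants and will be labeled with three codes". Each participant follows one of six sequences, and every sequence contains all three oils.

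**The concern.** The plan itself treats allergy or intolerance to the oils as a reason not to take part. The same reason applies to a child or other relative eating food cooked with the same oil. The rule is stated, its unit is the individual, and that unit is narrower than the group the article says will be exposed.

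What is at stake is the safety of people who are not enrolled. The Pistacia blend is where the question matters most. The Introduction presents the corn-canola blend with TBHQ as an example of oils already on the market, and Study design and population describes sunflower oil as widely used by Iranian families.

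**Working it through.** The plan gives no figure on this point, so the check sets the sections side by side.

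**Step 1: who eats the oil.** Study design and population and Compliance both say the participant and the family.

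**Step 2: who is screened for allergy.** Exclusion criteria covers individuals reporting an allergy or intolerance. Inclusion criteria asks for adults aged 20 to 50 years with metabolic syndrome and sets no household condition.

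**Step 3: apply the rules to a case.** Take a volunteer in that age range with metabolic syndrome, no allergy of their own, and a child with a known allergy to one of the oils. The inclusion criteria are met and no exclusion applies. Reading the rules as covering spouses changes nothing, because the child is not entered into the study on any reading.

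**Step 4: what that household receives.** Canola is in 3 of the 3 oils, corn in 2 and Pistacia in 1. Each intervention period lasts 8 weeks, so the Pistacia blend takes 8 of 3 × 8 = 24 intervention weeks. Over the six sequences, each oil takes each position in 2 of 6, a probability of 1/3 per period. A household that completes the trial is certain to receive the Pistacia blend. Only its timing is hidden.

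**Step 5: can the size be given?** Not from the document, which states no allergy rate and no household size. For illustration only, assume k = 1 to 3 non-enrolled members per household and a chance p = 0.1% to 1% per member of allergy or intolerance to any oil component, independent between members. The expected number of households with such a member is 72 × (1 − (1 − p)^k):

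- p = 0.001, k = 1: 72 × 0.001 = 0.07
- p = 0.01, k = 3: 72 × (1 − 0.99³) = 72 × 0.0297 = 2.1

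Both inputs are assumptions. The result counts households with an allergic member, not households where that member eats the oil. It also covers any component, not Pistacia alone. It shows only that the answer depends wholly on what is assumed, and it is not used as evidence.

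**The case against.** The strongest reply is that an eligibility list properly describes who may be a participant. On this view, advice to relatives belongs in the consent form or the full protocol, and neither is shown. That is fair as far as it goes. The full protocol may hold a household question, and the article cannot prove that it does not. The point survives because it does not rest on silence: the article states the allergy rule and its unit, and it states the wider supply of oil.

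A reader might infer that blinding leaves a family unable to protect an allergic relative. The documents do not support this. Every household gets all three oils, so only the order is concealed. The procedure is explained and consent is taken at the first visit. If that explanation names the oils, a family with a known allergy can decline or keep that person off all coded oil. Nothing in the article obliges a relative who is not enrolled to eat it. The intervention can be stopped at a participant's request, participants may leave without explanation, and there is a provision for unblinding. For canola, which is in every blend, the hidden order makes no difference at all.

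These routes depend on the family recognising the issue and acting on it. None of them is a question that the trial staff ask.

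**Conclusion.** The point holds as a limited gap in the eligibility rule: the stated allergy exclusion is narrower than the stated exposure, and a volunteer with an allergic child or other non-enrolled relative is eligible as written. This rests on reading the exclusion list as applying to people who enter the study, with spouses conceded.

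The size is unknown. A reader might take it that some of the 72 households are bound to be affected, but the document gives nothing from which to count them, and it is silent on how often these oils provoke reactions. Nor is there reason to infer a fault in the trial's inference: the sample size, the outcomes and the comparison of oils do not depend on this. It is a safety improvement worth considering because it costs so little.

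**What to change.** Extend the allergy and intolerance question at Visit 1, where Table 1 already places the eligibility assessment, the medical history and consent. Ask whether any household member who will eat the study oils has an allergy or intolerance to Pistacia, canola, corn or sunflower. Assignment to a sequence takes place during the run-in, so the answer is available before randomisation and before any study oil is supplied.

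If the answer is yes, either do not enrol the household, or enrol it only if that member uses separate non-study oil throughout, including the sunflower-oil phases where sunflower is the problem.

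The cost is one question at an existing visit, a few extra screen failures, or a separate bottle for one person. Randomisation, blinding and analysis stay as they are.

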### Recruitment and eligibility assessment

Recruitment will be taken place using advertisements and announcements at Endocrinology and Metabolism clinics and polyclinics of Shahid Sadoughi University of medical sciences, Yazd, Iran. The incidence of MetS in Yazd province is 56.1% [28]. The screening visit will be conducted by trained researchers for interested volunteers. During the first visit, the study procedure will be explained to participants, and informed consent will be obtained. Then, a questionnaire on socio-demographics and a 24-h physical activity recall will be completed for the participants. Also, anthropometric measurement, body composition, blood pressure measurement, laboratory assessment, and a 24-h food recall will be performed on the first visit by a trained nutritionist. Researchers will recommend the participants to maintain their physical activity all over the study period.

### Inclusion criteria

Adults aged 20 to 50 years with MetS [with at least three of these conditions: waist circumference > 102 cm in men and > 88 cm in women, systolic blood pressure > 130 mmHg or diastolic blood pressure > 85 mmHg, serum high-density lipoprotein (HDL) cholesterol < 40 mg/dl in men and < 50 mg/dl in women, serum triglyceride > 150 mg/dl, fasting blood glucose (FBG) ≥ 100 mg/dl] will be included in the present study [29].

### Exclusion criteria

Individuals reporting a history of cardiovascular disease, diabetes mellitus, any type of cancer, pancreatitis, liver disease, kidney disease, gastrointestinal disorders, history of changes in blood sugar and lipid-lowering pills over the past 3 months, changes in gastrointestinal medications less than 30 days before enrollment, weight changes over 3 kg during the 2 months prior to the study, allergy or intolerance to foods that will be used for the intervention, using alcohol consumption, using medication for hemostatic regulation (other than aspirin), taking systemic corticosteroids including androgen, phenytoin, erythromycin, taking drugs for COVID-19 including remdesivir, Interferon, actemra, favipiravir in the last 3 months, being pregnant, having intention to become pregnant, giving birth in the last 12 months, taking Omega-3 supplements more than 1 g/day, smoking more than 20 cigarettes a day, and those reluctance to follow the study protocol will be excluded from this study.

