### Physical activity and dietary intake assessment

The participants will be asked to keep their physical activity level and dietary intake constant during the study. The participant’s physical activity will be assessed using 3-day physical activity records (2 weekdays and 1 day of the weekend). The 3-day physical activity records will be filled in 6 times during the study (at the beginning and end of each intervention phase) (Table 1). The recorded data will be converted into metabolic equivalent-min/day (MET-minute/day) using the updated version of the compendium of physical activities [35]. Three-day dietary recalls (2 weekdays and 1 day of the weekend) will be used to measure dietary nutrient intake, including macro and micro-nutrients, at the beginning and the end of each phase of the intervention.

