### Assessment of medication use

Participants will be recommended to maintain their medication use during the study period. The researchers will also ask participants to inform them regarding the use and/or change of any medications during the study period since some drugs might have an impact on biochemical markers. To track their medication use, participants will be asked to bring all medications they consume during the intervention period at each visit. We will also ask them to report their usual medications (with their dosage) when contacted to assess the dietary intake data (Table 1).

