### Assessment of adverse events and provisions for post-trial care

We anticipate that the intervention oils will have no harm or adverse effect on the participants. However, adverse events, if any, will be reviewed by the trial steering committee and reported to the ethics subcommittee for monitoring the clinical trials at Shahid Sadoughi University. After completing the intervention periods, the blood test results, assessment of food intake, and physical activity will be interpreted for the participants and necessary recommendations will be provided if needed.

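### Diabetes is excluded only by reported history, although fasting glucose is measured at screening and has no upper limit for entry

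*Protocol article*

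**What the plan says.** All references are to the protocol article.

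- **Exclusion criteria.** The list opens with "Individuals reporting a history of cardiovascular disease, diabetes mellitus, any type of cancer". No measured glucose value appears in it. The only other wording on blood sugar concerns recent changes in blood-sugar-lowering pills.
- **Inclusion criteria.** Adults aged 20 to 50 years qualify with at least three of five components. One component is FBG of 100 mg/dl or more, with no upper bound.
- **Recruitment and eligibility assessment.** "The screening visit will be conducted by trained researchers for interested volunteers", and "laboratory assessment, and a 24-h food recall will be performed on the first visit by a trained nutritionist".
- **Intervention program, Table 1.** The individual rows for fasting glucose, triglyceride and HDL are marked at Visit 1. Run-in follows Visit 1, and "During the run-in period, the participants will be randomly assigned to one of the 6 rolling sequences".
- **Criteria for discontinuing or modifying allocated interventions.** The intervention stops if an exclusion criterion occurs or the participant asks. No glucose value is given.
- **Ethics and monitoring.** A data and safety monitoring committee (DSMC) reviews accumulating data for participant safety. No glucose criterion for an individual is stated.

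**The concern.** Listing diabetes as an exclusion shows the intention to study metabolic syndrome without diabetes. The test most likely to reveal an undiagnosed case is already done at screening, because the metabolic syndrome components cannot be counted without it. Yet the written rules use the result in one direction only: a high FBG helps a volunteer in, and no value keeps anyone out. The exclusion therefore works for diagnosed diabetes and misses undiagnosed diabetes, in a population selected partly for raised glucose.

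Two things are at stake. A person with a result that calls for clinical assessment may be entered into a long feeding study instead of being referred. And the enrolled population may include some of the people whom the exclusion was written to leave out.

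**Working it through.** The plan states no figure on this point, so the check is mainly a reading of the rules together.

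**1. Is the value available before randomisation?** Yes. Recruitment and eligibility assessment places laboratory work at the first visit. In Table 1 the general rows for blood sampling and biochemical assessment are unmarked at Visit 1, but the separate rows for fasting glucose, triglyceride and HDL are marked there. Randomisation takes place later, during the 4-week run-in.

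**2. Does any entry rule exclude on it?** Take a man with no known diabetes, a waist above 102 cm, triglyceride above 150 mg/dl and a Visit 1 FBG of *x* mg/dl.
- Inclusion: waist (1) + triglyceride (1) + FBG, met for every *x* ≥ 100 (1) = 3 of 5, so he is included.
- Exclusion: he reports no history of diabetes, so that clause does not apply, whatever *x* is.

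He is eligible for every *x* from 100 upwards. Because there is no ceiling at all, the result does not depend on which value is taken as the diabetic cut-off. A volunteer who already has three other components is eligible without the glucose component, and again no value of *x* excludes.

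**3. Does another section close the gap?** The discontinuation rule points back to the same exclusion list. The DSMC review covers accumulating study data and is not an entry rule. Neither names a glucose value.

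**4. How many people?** The documents give no share. Let *p* be the proportion of otherwise eligible volunteers with a diabetic-range Visit 1 FBG and no known diagnosis. The range for *p* is an assumption, used only to show scale.

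| *p* (assumed) | Expected among 72: 72 × *p* | Extra otherwise eligible volunteers to keep 72: 72/(1 − *p*), rounded up, minus 72 |
|---|---|---|
| 1% | 0.72 | 73 − 72 = 1 |
| 3% | 2.16 | 75 − 72 = 3 |
| 5% | 3.60 | 76 − 72 = 4 |

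**5. Does it disturb the primary comparison?** Little. Each participant is planned to receive all three oils and serves as their own control, and FBG is a secondary outcome. The planned sample size of 72 is unaffected.

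**The case against.** **The wording is loose, and the rule may be meant more broadly.** The opening phrase about reported history governs a list that also holds pregnancy, smoking and omega-3 dose, so it may not have been chosen with care. The discontinuation section treats exclusion criteria as things that can newly occur, which suggests that diabetes found at screening might also count. This is a fair reading of intent. It supports adding the clause, because no value is stated on which staff could act consistently.

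**Exclusion by known diagnosis is a common choice, and a glucose floor without a ceiling belongs to the definition of metabolic syndrome.** Both may be so. But a component definition does not have to serve as the exclusion rule as well, and here the measurement is already in hand.

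**Clinical oversight is not absent.** The DSMC includes an expert in clinical medicine and receives a report every 2 months, the study is coordinated at endocrinology and metabolism clinics, and Visit 1 includes a medical history. This makes it less likely that a very high value would go unnoticed. It does not alter the entry rule.

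**A stronger reading is tempting and does not stand.** The section on adverse events and post-trial care says: "After completing the intervention periods, the blood test results, assessment of food intake, and physical activity will be interpreted for the participants". Run-in, three periods and two washouts add up to 4 + 8 + 4 + 8 + 4 + 8 = 36 weeks, so a reader might infer that the protocol makes a participant wait about that long for a result, while "The participants will be asked to keep their physical activity level and dietary intake constant during the study" and "Participants will be recommended to maintain their medication use during the study period". The documents do not support this. The feedback sentence describes what is provided after the trial and does not say that results are withheld until then. A referral step for abnormal screening results may well be in the full protocol, which is not shown. Maintaining medication is only a recommendation, participants are asked to report any change, and the Discussion foresees a sensitivity analysis without those who change medication. Starting treatment is therefore not barred.

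**Conclusion.** The point holds for the entry rule. The stated criteria admit a volunteer with a diabetic-range Visit 1 FBG, no known diagnosis and enough other components, although the protocol means to exclude diabetes. This follows from the text alone and needs no particular cut-off.

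It is minor. The number affected is unknown; 0.7 to 3.6 among 72 rests entirely on the assumed 1% to 5%. The benefit is to participant safety and to enrolling the intended population, with little effect on the primary oil comparison and none on the sample size. It should not be read as a finding that the protocol delays feedback or prevents treatment.

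**What to change.** Add one clause to the Exclusion criteria: also exclude volunteers whose Visit 1 FBG meets a standard diagnostic cut-off for diabetes, and refer them for care before randomisation. The investigators should fix the value and write it down, since the documents give none. The change applies at entry only and stops no one after randomisation.

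The cost is a few more screen failures: about 1 to 4 more otherwise eligible volunteers screened if the share is 1% to 5%. No new sample, visit or assay is needed.

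On the stated schedule, interventions end by 20 March 2023. Counting back 36 weeks puts the latest start of run-in at about 11 July 2022, before the January 2023 protocol version. If enrolment has closed, the Visit 1 values on file can be checked and anyone affected referred.
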